### Randomization

Participants are randomized by health care zone. Patients in the low-fructose diet intervention group (LFDI) are assigned to health centers in the western zone of Tenerife island, and patients in the Canary Islands Health Service standard-diet control (SDC) group are assigned to the eastern zone of the island. This randomization system is used to prevent contamination bias. If patients randomized to both groups attended the same health center this source of bias would be difficult to avoid because many patients in the LFDI group are likely to have relatives or friends in the SDC group, and vice versa. Contamination could also occur between staff members at a given health center. Sixteen primary health centers are participating in this study; all of them belong to the same health care administration district (Gerencia de Atención Primaria de Tenerife). Given that the total area of the island of Tenerife is relatively small, the characteristics of the population served by all health centers are assumed to be similar. The longest distance between participating health centers is 64 km. All centers and staff provide the same suite of services. The variations between centers in the catchment population assigned and the numbers of patients under each staff physician’s and nurse’s care are similar. We therefore do not anticipate between-group differences in the baseline data or systematic biases in the results of the care provided at different centers.

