**Methods/design:**

This field trial is located at primary care centers. The participants are adults aged 29 to 66 years, with a Body mass Index (BMI) between 29 and 40.99 kg/m^2^ and without diabetes. To date, 245 participants have been assigned randomly to the low-fructose diet intervention group (LFDI) at health centers in the western health service zone of Tenerife island, and 245 to the standard-diet control group (SDC) at health centers in the eastern health service zone. Recruitment is opportunistic and is carried out by physicians and nurses at participating health centers. Initially (baseline), and after 24 weeks of intervention, dietary records, physical activity, waist circumference, BMI, blood pressure, fasting blood glucose and insulin concentrations (HOMA2-IR) and lipid profile are recorded; blood glucose and insulin and lipid profile are also recorded 2 h after a 75-g glucose overload. After 48 weeks (24 weeks after the intervention), fasting blood samples are again obtained and a physical examination is performed. All tests and measures are repeated and recorded except dietary records, physical activity and oral glucose overload. Low-fructose diets are designed by calculating free and total (free + fructose associated with sucrose) fructose contents in standard diets, and removing foods with a fructose content in the highest quartile for the amounts in the standard diet.

Participants in both groups are prescribed a diet that contains 30 to 40% less than the participant’s energy requirements. The primary endpoint is change in HOMA2-IR between baseline and week 24, and other outcomes are change in HDL-cholesterol, LDL-cholesterol, triglycerides , waist circumference to height ratio and BMI. The secondary endpoint is change in HOMA2-IR between week 24 and week 48 together with the outcomes noted above. Comparisons between groups for variables used to indicate IR levels are done with a Student’s *t* test for unpaired variables or the Mann-Whitney *U* test if the distribution is not normal. Multivariate regression models will be used to control for confounding factors not accounted for in the study design, and for independent prognostic factors.

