Most trials designed to reduce fructose consumption have involved children and adolescents as frequent consumers of sugar-rich beverages. A controlled double-blind trial that enrolled children showed that a dietary education programs designed to reduce sugar and fructose consumption by substituting low-calorie sweetened beverages for sugar-containing beverages had beneficial effects on Body Mass Index (BMI) [12]. A randomized trial that followed with overweight and obesity for 2 years found that the increase in BMI was smaller in participants who consumed fewer sugar-sweetened beverages [13]. Neither of these trials investigated IR, and calorie intakes in the intervention group were lower than in the control group. Another trial with African-American and Latino adolescents found that reducing the consumption of added sugar improved insulin sensitivity even when body weight or body fat was not reduced [14]. In that study, calorie intake in terms of kcal/day was again higher in the control group than in the two intervention groups (nutrition education, and nutrition education plus strength training). The only study in adults that we are aware of was designed to analyze the effect of decreased fructose consumption on body weight and IR [15]. This study compared two isocaloric diets with no added sugars but containing different amounts of fructose (≤20 g versus 50–70 g). The decrease in BMI was greater in the latter group, and IR (HOMA) was also lower although the difference between groups was not statistically significant (*p* = 0.12).

In light of the gaps in our current knowledge, we designed a field trial to test the effects of decreased fructose consumption on IR under real-life conditions in participants who consume an isocaloric diet.

We describe here a single-blind, multicentre, randomized controlled field trial lasting 24 weeks that is being carried out at primary health care centers, designated the DISFRUTE (DISminución de la FRUctosa en TEnerife, i.e., Decrease in fructose in Tenerife) study. The aim of the trial is to determine whether a decrease in dietary free or sucrose-associated fructose is effective in decreasing IR.

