### Recruitment

Physicians and nurses recruited participants with an opportunistic method. To facilitate recruitment we designed a digital application for electronic medical records that make it possible to identify patients who could hypothetically be recruited on the basis of our inclusion and exclusion criteria. The first screen of the electronic medical record displays an alert indicating that the patient is potentially eligible for inclusion. The nurse or physician explains the nature and aims of the study to the patient, and if the patient expresses interest in taking part, the physician asks three questions about their motivation. If the patient answers “yes” to all three questions the nurse or physician asks them to sign the Informed Consent Form (see Additional file 1), and then gives the patient a brief Information Pack that includes four pages of a food diary in which the patient is asked to record all foods and beverages consumed each day during a 4-day period that includes one weekend day or holiday. The Information Pack also includes a sheet with instructions on how to record foods and beverages in the food diary (see Additional file 2). On the day that the patient signs the Informed Consent Form, an appointment is scheduled to review the food diary and complete the Case Record Form (CRF). At this appointment the physician or nurse carefully reviews all four daily food diary sheets with each participant to ensure accuracy regarding the types, sizes and portions of each food and beverage. During this appointment the participant is interviewed about their physical activity and the information provided is entered by the physician or nurse into the Minnesota Leisure-time Physical Activity Questionnaire form. Body weight, height and waist circumference are recorded, and blood pressure is measured twice and recorded as the average of the two values. At the end of this appointment the participants is given an appointment for a blood test (week 0). The blood sample is provided after an overnight fast, and is used to measure plasma glucose, insulin and lipid concentrations (total, LDL- and HDL-cholesterol and triglycerides). At week 0 we also record thyroid stimulating hormone (TSH), total thyroxine (T_4_) if TSH is altered, and urinary microalbumin/creatinine ratio (to rule out relevant thyroid or kidney disease). All participants undergo an oral glucose overload test (75 g) to record blood insulin, glucose and lipids 2 h later. All participating health center staff are reminded to use the same equipment in each appointment to record blood pressure, weight and height. All devices are calibrated regularly by the Canary Islands Health Service. Nonstretchable measuring tape is used to record waist circumference by situating the tape halfway between the lower margin of the last rib and the iliac crest with the participant breathing normally.

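### Diet is allocated by health zone, one zone per arm, so diet and zone cannot be separated and the trial does not have the participant-level randomization it claims

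*Protocol article*

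**What the plan says.** The Abstract (Methods/design) reports that "245 participants have been assigned randomly to the low-fructose diet intervention group (LFDI) at health centers in the western health service zone", with a control group of the same size in the eastern zone. The end of the Background calls the study a "single-blind, multicentre, randomized controlled field trial lasting 24 weeks", and the Design section repeats the label.

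The Randomization section gives the mechanism: "Participants are randomized by health care zone". It continues: "Patients in the low-fructose diet intervention group (LFDI) are assigned to health centers in the western zone of Tenerife island", while patients in the "standard-diet control (SDC) group are assigned to the eastern zone of the island". The stated reason is to prevent contamination between relatives, friends and staff who share a health center. Sixteen centers take part; their split between zones is not given. On comparability, the section argues from the small size of the island that "the characteristics of the population served by all health centers are assumed to be similar". It adds the shared administration and similar services, and expects no baseline differences or systematic bias.

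The Recruitment section says: "Physicians and nurses recruited participants with an opportunistic method". An alert in the electronic record flags possible candidates. The nurse or physician then explains the study, three motivation questions are asked, and consent is taken.

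The Statistical analysis section compares groups with an unpaired t test or a Mann-Whitney U test on participants. Regression models are to look for confounders; the candidates listed are calorie intake, nutrients other than fructose, and physical activity. Adjustment for baseline is conditional on a difference being detected in HOMA2-IR, a nutrient intake or physical activity.

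**The concern.** Randomization earns its place by making the arms comparable apart from chance and by justifying the p-value. Neither follows when a whole zone receives one diet and the only other zone receives the other. A west-east difference in population, habits, staff or style of care that affects the 24-week change in HOMA2-IR would become part of the estimated diet effect, and nothing in the data could show which part it was.

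Recruitment adds a second route. Center staff decide opportunistically whom to approach, and their arm follows from their zone, so the type of patient entered can differ by arm.

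At stake is how a significant result would be read. A reader told that participants were randomly assigned will credit the diet, whereas this design supports only a comparison of two zones that were given different diets.

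**Working it through.** **1. Is there a random step for participants or centers?** Set side by side, the Randomization section ties diet to zone, and the Recruitment section enters patients at participating centers. The center a patient attends thus fixes the diet. Randomizing patients first and then sending them to a zone does not fit this recruitment, nor the argument about relatives attending the same center. No draw of participants, centers or zones is described.

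**2. Can diet and zone be separated?** Let D = 1 for low-fructose and Z = 1 for west. By design D = Z for every participant, so a model with both terms has two identical columns and cannot estimate both. A center term does not help, because centers are nested within zones. With one zone per arm there are 2 − 2 = 0 degrees of freedom for between-zone variation.

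**3. What if the zones were drawn by lot?** Two zones, one per arm, give C(2,1) = 2 allocations. The smallest randomization p-value is 1/2 = 0.5 one-sided and 1.0 two-sided. For contrast, 16 centers randomized 8:8 would give C(16,8) = 12,870 allocations and a smallest two-sided p of 2/12,870 ≈ 0.00016.

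**4. Numbers per arm.** The Design section gives 245 per group with 20% loss, so 245 × (1 − 0.20) = 196 completers. The 245 cannot be independently reproduced because no SD is stated. Solving backward for a 4 kg difference, two-sided 0.05 and 80% power gives SD = 4 × √(196/2) / (1.960 + 0.842) ≈ 14.1 kg. Nothing below depends on that SD. The stated intention-to-treat analysis uses the latest available measurement for non-completers, which points to 245 analysed per arm, so both sizes are shown.

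**5. Illustration of size.** Assumptions: no diet effect; a zone difference b in HOMA2-IR change, in SD units of the analysed change; an unadjusted two-sided test at 0.05. The values of b are assumed; the documents give none.

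SE = √(2/n): √(2/196) = 0.1010 and √(2/245) = 0.0904.

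False-positive rate = 1 − Φ(1.96 − b/SE) + Φ(−1.96 − b/SE).

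Worked case, b = 0.10 and n = 196: b/SE = 0.990, so 1 − Φ(0.970) + Φ(−2.950) = 0.166 + 0.002 = 0.168.

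| Assumed b (SD) | 196 per arm | 245 per arm |
|---|---|---|
| 0.10 | 16.8% | 19.8% |
| 0.15 | 31.8% | 38.2% |
| 0.20 | 50.8% | 60.0% |

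The nominal rate is 5%. For a fixed b, more patients raise the rate, because the test becomes more certain of a difference that is not due to diet.

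**6. Does the stated analysis respond?** The baseline adjustment is triggered by a detected difference in three kinds of variable. Socioeconomic class is recorded (Data recording and analysis) but is not named, and neither are age, sex or BMI.

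**The case against.** The strongest defence has five parts.

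- *The layout is disclosed.* The zones are named in the same sentence of the Abstract that speaks of random assignment, and the Randomization section opens with the zone. This stands: nothing is hidden. But disclosing zone allocation does not make it random assignment of participants.
- *Contamination is a real risk.* It is. The argument, however, concerns people who share a health center. It supports allocation by center and does not require all centers in a zone to have the same diet.
- *The endpoint is a change from baseline, and regression is planned.* Stable differences in HOMA2-IR level largely cancel, and measured confounders can be adjusted for. This stands as a reduction of bias. Differences in change, and anything unmeasured that goes with zone, remain. An analysis plan that is not shown could add covariates but could not separate zone from diet.
- *Recruitment has safeguards.* An electronic alert flags eligibility, every candidate is asked the same motivation questions, and staff prescribing standard diets do not know which foods the other diets omit. That staff knew their arm when inviting patients is an inference; the Recruitment section does not say so. The safeguards lessen selective invitation but do not exclude it.
- *A condensed article may omit a draw of zones.* It may. The fix therefore asks for a statement and does not presume that no draw took place.

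A reader might also infer that the Discussion already draws an unsupported causal conclusion. It does not: it states a hypothesis and a conditional prospect, and the trial is still running.

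**Conclusion.** The point holds. Diet and zone are completely aliased, and the description of participants as randomly assigned in a randomized controlled trial claims a property the design lacks. This follows from the text alone, without numerical assumptions, and no analysis can repair it. It should be corrected before results are reported.

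The false-positive rates, about 17% to 51% with 196 per arm and 20% to 60% with 245, rest on assumed zone differences of 0.10 to 0.20 SD and an unadjusted test. They show how small a zone difference would matter and are not estimates for this trial. A reader might infer that the zones do differ, or that the result will be biased. The documents do not show that; they show only that the design cannot rule it out.

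**What to change.** - In the Abstract, Background and Design, replace the wording about random assignment and a randomized controlled trial with: *allocated by health zone (two zones, 16 centers)*. State whether the zones were drawn at random and, if so, how.
- State as a limitation that zone and diet are confounded, and limit any conclusion to a zone-allocated comparison.
- Always adjust the primary estimate for baseline variables already collected: HOMA2-IR, age, sex, BMI, socioeconomic class, calorie intake and physical activity. Delete the condition that a difference must first be detected. Say that this reduces zone confounding but does not remove it.
- Report baseline and outcome data by center.

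Two further steps look natural but should not be relied on. Counts of patients alerted and invited per center would help, but no logging of them is described, so they cannot be treated as data in hand. The spread between centers within a zone does not bound a difference between zones, so it is no yardstick for one.

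Recruitment began in May 2014, so this fix leaves the allocation as it is. The cost is rewording, a fixed covariate list and tables from data already collected. The downside is a more modest claim.

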### Recruitment

Physicians and nurses recruited participants with an opportunistic method. To facilitate recruitment we designed a digital application for electronic medical records that make it possible to identify patients who could hypothetically be recruited on the basis of our inclusion and exclusion criteria. The first screen of the electronic medical record displays an alert indicating that the patient is potentially eligible for inclusion. The nurse or physician explains the nature and aims of the study to the patient, and if the patient expresses interest in taking part, the physician asks three questions about their motivation. If the patient answers “yes” to all three questions the nurse or physician asks them to sign the Informed Consent Form (see Additional file 1), and then gives the patient a brief Information Pack that includes four pages of a food diary in which the patient is asked to record all foods and beverages consumed each day during a 4-day period that includes one weekend day or holiday. The Information Pack also includes a sheet with instructions on how to record foods and beverages in the food diary (see Additional file 2). On the day that the patient signs the Informed Consent Form, an appointment is scheduled to review the food diary and complete the Case Record Form (CRF). At this appointment the physician or nurse carefully reviews all four daily food diary sheets with each participant to ensure accuracy regarding the types, sizes and portions of each food and beverage. During this appointment the participant is interviewed about their physical activity and the information provided is entered by the physician or nurse into the Minnesota Leisure-time Physical Activity Questionnaire form. Body weight, height and waist circumference are recorded, and blood pressure is measured twice and recorded as the average of the two values. At the end of this appointment the participants is given an appointment for a blood test (week 0). The blood sample is provided after an overnight fast, and is used to measure plasma glucose, insulin and lipid concentrations (total, LDL- and HDL-cholesterol and triglycerides). At week 0 we also record thyroid stimulating hormone (TSH), total thyroxine (T_4_) if TSH is altered, and urinary microalbumin/creatinine ratio (to rule out relevant thyroid or kidney disease). All participants undergo an oral glucose overload test (75 g) to record blood insulin, glucose and lipids 2 h later. All participating health center staff are reminded to use the same equipment in each appointment to record blood pressure, weight and height. All devices are calibrated regularly by the Canary Islands Health Service. Nonstretchable measuring tape is used to record waist circumference by situating the tape halfway between the lower margin of the last rib and the iliac crest with the participant breathing normally.

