### Study participants

Four hundred and ninety patients who participate voluntarily; our intention is to include at least 40% men.

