#### Inclusion criteria

Adults, aged between 29 and 66 years, BMI between 29 and 40.99 kg/m^2^.

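### Recruiting staff very probably know their center's diet, choose whom to approach and apply a motivation screen missing from the criteria, so enrolled patients can differ by arm; the expected baseline balance ignores this

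*Protocol article*

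**What the plan says.** Allocation (Protocol article, Randomization): "Participants are randomized by health care zone". The consequence is spelled out: "Patients in the low-fructose diet intervention group (LFDI) are assigned to health centers in the western zone of Tenerife island", and the standard-diet control patients belong to the eastern zone. "Sixteen primary health centers are participating in this study".

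Entry (Recruitment): "Physicians and nurses recruited participants with an opportunistic method". An alert in the electronic record flags possible candidates. The nurse or physician explains the study, and the physician asks an interested patient three questions about motivation. "If the patient answers “yes” to all three questions the nurse or physician asks them to sign the Informed Consent Form".

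Stated criteria (Inclusion criteria): "Adults, aged between 29 and 66 years, BMI between 29 and 40.99 kg/m^2". Neither this section nor the Exclusion criteria mentions motivation. Under Study participants the only target for composition is "our intention is to include at least 40% men", set for the 490 as a whole.

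Expectation (Randomization): "We therefore do not anticipate between-group differences in the baseline data or systematic biases in the results of the care provided at different centers".

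Analysis (Statistical analysis): baseline adjustment follows if the groups are found to differ in HOMA2-IR, a nutrient intake or physical activity. Regression models are also planned for confounders and for prognostic factors that the design does not control.

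**The concern.** When allocation is by zone and recruitment comes afterwards, nothing conceals the arm from the person who decides whom to invite. Staff offering a new diet and staff offering usual care may approach different patients, or present the study differently before the motivation questions are put. This is a separate matter from whether west and east Tenerife differ as populations: two identical populations can still yield different samples.

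At stake is the primary comparison, the change in HOMA2-IR to week 24. If one arm enrols patients more ready to follow any restricted diet, its HOMA2-IR may fall further for reasons unrelated to fructose. Motivation is not recorded as a covariate. Everyone enrolled has also answered yes to all three questions, so the screen leaves no variation to adjust for.

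**Working it through.** **Do recruiters know the arm?** The article does not say so outright. Three places point the same way.
- Randomization: the zone determines the diet, so a center's arm is settled in advance. The worry there about contamination between staff of one center presupposes that staff know what they deliver.
- Data recording and analysis: collaborating staff were trained in delivering the dietary interventions at a session two months before field work.
- Intervention: prescribers of the standard diet are kept unaware only of which foods the other diet drops, not of which diet they themselves prescribe.

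The Design section calls the trial single-blind without saying who is blinded, so it does not contradict this.

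**Do they have discretion?** The alert standardizes who is flagged. No rule in the article requires that every flagged patient, or consecutive ones, be approached. The motivation questions then act as an entry condition outside the listed criteria.

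**Does the balance argument cover this?** Its grounds are a small island with populations assumed similar, the same services, and similar caseloads. All concern who is available to be recruited; none concerns who is chosen or who passes the screen.

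**Does the analysis cover it?** Only in part. Adjustment for baseline HOMA2-IR, nutrient intake and physical activity depends on a difference being detected. The general regression clause could take in age or sex, but does not name them, and cannot reach motivation.

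**The pooled target.**
- Pooled: 0.40 × 490 = 196 men.
- One split that meets it: 123 + 73 = 196, with 123/245 = 50.2% and 73/245 = 29.8%, a gap of 50/245 = 20.4 percentage points.
- Per arm: 0.40 × 245 = 98 men.

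The split is hypothetical. It shows only that the target does not protect balance between arms.

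**Sensitivity to a small selection effect (assumed values).** Suppose that the diet has no effect and that selection shifts the mean change in HOMA2-IR by b standard deviations. With n per arm, a two-sided 5% test and clustering ignored, the standardized shift is d = b/√(2/n), and the rejection rate is 1 − Φ(1.96 − d) + Φ(−1.96 − d). For b = 0.10 and n = 245, d = 0.10/0.0904 = 1.107, which gives 19.8%.

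| Assumed b (SD) | n = 245 per arm | n = 196 per arm (20% loss) |
|---|---|---|
| 0.05 | 8.6% | 7.9% |
| 0.10 | 19.8% | 16.8% |
| 0.20 | 60.0% | 50.8% |
| 0.30 | 91.3% | 84.4% |

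The values of b are not in the documents. The table shows what a shift would do, not how large the shift is.

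**The case against.** The strongest reply is that the motivation screen is a fixed rule. The patient answers, three affirmative answers lead to consent, and no difference between arms is described. A common gate may even narrow differences in motivation. This stands as far as it goes: staff are not shown to rate motivation. It does not answer who is approached, or how the study is presented before the questions.

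Second, the two offers are much alike: energy-restricted diets, the same visits and tests, materials of identical appearance, and advice in both arms to avoid added sugar. This makes strong differential selection less likely, but does not exclude it.

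Third, the plan does provide some adjustment, including for baseline HOMA2-IR. That is true, and it partly answers the concern, but it is conditional and covers few variables.

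Fourth, the wording of the questions may be in an additional file that is not shown. The point needs only that the screen decides entry and is absent from the stated criteria.

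Two stronger readings are tempting. A reader might infer that staff pick patients by insulin resistance. The insulin test and the glucose overload come after consent, and nothing shows that recruiters have HOMA2-IR when they approach a patient. A reader might also infer that a sex imbalance would distort the diets prescribed in the two arms. Energy is set relative to each person's own requirement, with sex already allowed for, and calorie intake is a named potential confounder. Neither reading is supported. The 40% figure is also an intention, not a binding quota.

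**Conclusion.** The concern holds as a statement of possibility: entry can differ by arm through unconcealed recruiters, and the article's expectation of no baseline differences does not consider it. The documents do not show that selection has occurred, and its size cannot be computed from them. The conclusion rests on one inference, that staff know their own center's diet, for which the article leaves little other reading. It also rests on the absence of any rule for consecutive or complete approach of flagged patients. It merits correction because the plan as written leaves this route of bias unchecked and denies it on grounds that do not bear on it.

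**What to change.** 1. For any remaining enrolment, approach flagged patients consecutively at each center, under the same rule in both zones, and apply the 40% men target within each arm (at least 98 of 245). This may come too late: the Abstract reports 245 already assigned to each group, although Intervention and Trial status describe recruitment or the trial as still under way.
2. As far as the application retains the data, tabulate flagged, approached, screened-out, refusing and enrolled patients by center and arm, and compare them on age, sex and BMI. The article describes an alert, not a log, so availability has to be checked.
3. Adjust the primary comparison for baseline HOMA2-IR, age, sex and BMI whether or not a baseline difference is detected. This will not remove differences in motivation, so items 2 and 4 are still needed.
4. State the motivation screen as an entry criterion and limit the conclusion to patients who pass it. Replace the sentence expecting no baseline differences or systematic biases with one that acknowledges possible selection by recruiters who know the arm.

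The cost is some staff time, possibly slower recruitment of men in one arm, a short amendment and one extra table. Items 2 to 4 remain possible after enrolment closes.
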